## Methods

### Objectives and hypotheses

The current study will test the implementation of the MHRN suicide risk model in behavioral health clinics to facilitate identification, recognition, and engagement in supportive suicide prevention services among individuals estimated to be at risk for suicide. The study’s main aim is to examine the effectiveness of a suicide risk model on fatal and non-fatal suicide attempts (primary outcome). The secondary outcome analyses examine the following questions: Are patients who receive care in the behavioral health intervention clinics more likely to be referred to and receive supportive outpatient behavioral health services than patients in usual care clinics? Are they more likely to receive supportive services sooner after risk recognition than they would have before the risk models were used, or earlier than patients in usual care clinics? Are they less likely to require crisis services and less likely to attempt suicide? Specifically, we will test the hypothesis that the risk model will lead to a reduction in suicide attempts (primary outcome) and an increase in referrals to, and receipt of, supportive outpatient services (secondary outcome).

In secondary analyses, we will determine whether implementing a suicide risk model into a suicide prevention care model improves identification of patients at risk for suicide attempt (suicide screening practices); that is, whether the enhanced identification using a risk model improves upon self-reported risk screening relied upon in usual care. Specifically, does the risk model (intervention) identify additional patients for screening who would not be identified in the course of usual care? How many additional patients are recognized (complete a risk assessment)? We hypothesize that the risk model may identify people who miss or refuse screening, deny risk because they do not believe themselves to be at risk or feel ambivalent, or deliberately conceal their risk. We will test the hypothesis that the suicide risk model implementation will improve identification and recognition of patients at increased risk of suicide attempt compared to usual care.

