### Study measures and effectiveness outcomes

The primary outcome measure is fatal or non-fatal suicide attempt (binary yes/no) within 90 or 180 days of a behavioral health visit as measured using diagnosis codes for intentional self-harm (International Statistical Classification of Diseases and Related Health Problems, Tenth Revision [ICD-10] codes X60-X84; Y87.0). Suicide deaths will be ascertained from government mortality records. The denominator will be the total number of visits to behavioral health clinics and the numerator will be reported as the number of suicide attempts per 1000 visits. In addition to the primary outcome, we will examine proximal outcomes and crisis utilization measures. Proximal outcomes include measures of engagement with services documented in the EHR within the observation period. These are defined as: evidence-based suicide prevention interventions (safety planning, lethal means counseling, or caring contacts) on or after the risk identification (index) encounter, an outpatient encounter (includes telephone, virtual, and office visits) by a behavioral health clinician or psychiatrist subsequent to the index encounter, any contact with behavioral health within seven or 14 days of the index visit (includes phone calls, letters, patient portal messages, or other caring contacts in addition to encounters described above), frequency of contacts, latency to next encounter after index, and persistence in psychotherapy defined as no gap in psychotherapy visits > 90 days during the observation period. Crisis utilization measures include any encounters in the emergency department or inpatient stays subsequent to the index encounter within 90 days and 180 days.

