These models will also be used to test mediators/mechanisms, given that we hypothesize that identification alone will not reduce suicide outcomes but rather increase the number of people receiving suicide intervention, which could lead to improvement (i.e., decrease) in suicide outcomes. Mechanisms include interaction with the alert and initiation of assessment, which starts the outpatient care pathway. We will also stratify analyses by health system site, and test for mental health diagnoses and prior suicide attempts as moderators. Importantly, we will exclude ‘training’ months for each phase of clinic implementation from the main analyses, since clinicians and patients may be partially exposed as the models are implemented and clinicians trained. In a secondary set of analyses, we will explore potential heterogeneity in treatment effects between clinics. Here we will conduct additional analyses to test within cluster comparisons of exposed and unexposed periods.

To examine the effectiveness of a suicide risk model on health service engagement and suicide attempt outcomes, we will start with similar descriptive and GLMMs analyses proposed previously for identification and recognition. The analyses here will focus on each unique health service engagement (supportive and crisis encounters separately) and suicide attempt outcomes, stratified by exposed (intervention) versus unexposed (control) groups. Suicide attempts will be captured by health system records using ICD-10 diagnosis codes occurring within the same 90-day and 180-day time periods. We will also use a Kaplan-Meier method and Cox-proportional hazards models to examine time-to-event for health service engagement and suicide attempts, with statistical adjustment for clinical and demographic factors. Individuals will be censored at the time of death or at 180 days past the index visit. We will again add terms for calendar month as well as site to account for variation by season and health system.

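### As written, the supplementary time-to-event analysis censors suicide deaths that the primary outcome counts as events

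*Protocol article*

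**What the plan says.** *Study measures and effectiveness outcomes* defines the endpoint: "The primary outcome measure is fatal or non-fatal suicide attempt (binary yes/no) within 90 or 180 days of a behavioral health visit". It measures this with ICD-10 codes for intentional self-harm and adds a second source: "Suicide deaths will be ascertained from government mortality records". *Objectives and hypotheses* likewise names fatal and non-fatal attempts together as the main aim.

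*Analysis plan for effectiveness outcomes* describes capture of the same outcome as follows: "Suicide attempts will be captured by health system records using ICD-10 diagnosis codes occurring within the same 90-day and 180-day time periods". Mortality records are not mentioned there. Generalized linear mixed models (GLMMs) come first, and a second set of methods is then added: "We will also use a Kaplan-Meier method and Cox-proportional hazards models to examine time-to-event for health service engagement and suicide attempts". One censoring rule covers both kinds of endpoint: "Individuals will be censored at the time of death or at 180 days past the index visit".

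Two other sections bear on the data source. *Data sources* says the primary and secondary outcomes come from EHR and claims data, and *Potential study limitations* describes attempt ascertainment in the same terms. Only the outcome section names mortality records.

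**The concern.** When the endpoint includes a fatal event, a rule that censors at any death removes part of the endpoint. A patient who dies by suicide without an earlier coded attempt contributes event-free time up to the death and then leaves the risk set. Here the reason for censoring is the outcome itself, so the usual assumption that censoring is unrelated to the outcome fails by construction.

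The Kaplan-Meier curve and the Cox hazard ratio would then describe coded attempts, not the composite in the outcome section. If the intervention affected deaths differently from non-fatal attempts, in either direction, the hazard ratio would not show it. The component lost is the most severe one.

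**Working it through.** **1. The stated rules, applied to each type of patient**

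| Patient within 180 days of the index visit | Outcome definition | Time-to-event rule as written |
|---|---|---|
| Non-fatal attempt, coded | Event | Event |
| Fatal attempt, self-harm code recorded before death | Event | Event |
| Suicide death, no earlier self-harm code | Event, from mortality records | Censored at death |
| Death from another cause | Not an event | Censored at death |

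The sections disagree only in the third row.

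**2. The plan's own event count**

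*Sample size and power analysis* gives about 395,000 patients, a 0.6% attempt rate within 90 days, and 2,370 events.

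395,000 × 0.006 = 2,370. The figure reproduces exactly.

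The document gives no event count for the time-to-event analysis, which runs to 180 days. I use 2,370 only as a scale and assume that it includes fatal attempts.

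**3. Fatal share**

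No share is given for the trial. The only related figures are the 2022 national ones in the *Background*: more than 49,000 suicide deaths and 1.6 million adults attempting.

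- Deaths already within the attempt count: 49,000 / 1,600,000 = 3.06%, and 2,370 × 0.0306 ≈ 73.
- Deaths additional to it: 49,000 / (1,600,000 + 49,000) = 2.97%, or about 3%, and 2,370 × 0.03 ≈ 71.

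These figures set deaths at all ages against attempts by adults, and they are national, so the share in the trial could differ. Over an assumed range:

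| Assumed fatal share | Events that could be censored, of 2,370 |
|---|---|
| 3% | 71 |
| 5% | 118 |
| 10% | 237 |
| 20% | 474 |

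Each count is the maximum at its share, because it supposes that no fatal attempt was coded before death.

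**4. Effect on the hazard ratio (illustration)**

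Let f be the fatal share among control events, and suppose that all fatal attempts are censored. Then approximately:

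composite HR = (1 − f) × HR(non-fatal) + f × HR(fatal)

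Assume HR(non-fatal) = 0.80. The censored analysis shows 0.80 whatever happens to deaths.

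| HR(fatal) | Composite HR, f = 3% | Composite HR, f = 20% |
|---|---|---|
| 0.6 | 0.794 | 0.76 |
| 0.8 | 0.80 | 0.80 |
| 1.0 | 0.806 | 0.84 |
| 1.2 | 0.812 | 0.88 |

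At 3% the composite moves by about 0.01 at most. It moves noticeably only if the fatal share is much larger and the two effects differ.

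**The case against.** The best defence is that the censoring sentence serves two endpoints. For service engagement, censoring at death is ordinary. For attempts, censoring applies only to people who have not had the event, and since the outcome section makes a fatal attempt an event, a suicide can be read as an event on that day. This reading is possible and may be what was meant. However, nothing in the analysis section says so, and the capture sentence there omits the source that would identify such deaths. A programmer following that section would censor them.

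A reader might also infer more than the documents support:

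- **That attempts come from diagnosis codes alone.** The analysis section omits mortality records but does not exclude them, and the outcome section names them.
- **That the primary result loses fatal attempts.** The primary outcome is binary and analysed by GLMM, and the censoring rule does not apply to it. The capture sentence does follow the GLMM text, so the source wording needs aligning there too, but no loss from the primary analysis is shown.
- **That half of the outcome is lost.** Fatal attempts are one of two named components. The document's own figures suggest about 3% of events.
- **That these patients are treated as event-free to 180 days.** They are censored at death, which is a different error.
- **That the Cox model ignores secular trend.** The same section says that all analyses adjust for time because the proportion of exposed clinics rises, so this does not stand.
- **That the Cox standard errors ignore clinics.** The Cox description lists no clinic term, but an article may leave that to the analysis plan. It is at most a point to clarify.

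**Conclusion.** The conflict is real but limited. As written, the Kaplan-Meier and Cox analyses of suicide attempts censor suicide deaths that have no earlier self-harm code, although the outcome section counts them as events. The resulting hazard ratio would not reflect effects on those deaths.

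On the national figures, up to about 71 to 73 of 2,370 events are affected. This rests on the national share applying to these patients and on no fatal attempt being coded before death. The true share is unknown, and the 3% to 20% range above is an assumption. The analysis concerned is supplementary. It should be corrected before the analysis is run, but it does not undermine the primary comparison.

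**What to change.** In *Analysis plan for effectiveness outcomes*:

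1. State that in the time-to-event analysis of attempts, a suicide death found in mortality records is an event on the date of death, unless a coded attempt has already been counted.
2. State that only non-suicide deaths are censored, giving a cause-specific hazard, or are treated as competing events. Give the rule for service engagement separately; censoring at death can stay there.
3. Name mortality records as a source of attempts alongside the ICD-10 codes, and say the same in *Data sources*, so that both sections match the outcome definition.
4. Optionally, state how the Cox model handles clinics (a frailty term or clinic-robust variance), if the analysis plan does not already do so.

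The cost is a few sentences and a small change to the event and censoring variables. Ascertainment of suicide deaths is already planned, so no new data source is needed.

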### Overview of study design

The current study will use a hybrid type I effectiveness-implementation approach to test implementation of an EHR-derived suicide risk model to facilitate identification, recognition, and engagement in supportive suicide prevention services among individuals who are estimated to be at risk for suicide and receiving services in behavioral health clinics at the participating health systems. This includes a stepped wedge cluster randomized trial design [31, 32] with randomization of behavioral health clinics into three waves across the three participating health systems. This design offers a novel approach to studying service delivery interventions as it provides a baseline period without implementation followed by random and sequential crossover of clinics from usual care control to intervention until all participating clinics are exposed. All clinics will have a pre-implementation phase (baseline period). Within that, just prior to implementation, health systems will train clinicians. Clinician training materials will be provided but sites will operationalize the training according to local customs and resources. Differences in training rigor provide additional variability as they may partially account for acceptability or feasibility. Implementation begins when each randomized clinic (stratified by site) transitions from usual care to running the risk model so clinicians can observe the risk indicator (the intervention is the enhanced care model with the suicide risk model and associated clinician notification). Analyses will examine within and between clinic variation in outcomes and account for time since implementation. This design allows implementation of the intervention at all clinics during the study period, a requirement of our clinical stakeholders; similar designs have been used in other suicide prevention trials [33, 34].

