### Sample size and power analysis

We anticipate including > 50 clinics and approximately 395,000 unique behavioral health patients across three sites over a 2.5-year period, leading to over 1 million patient visits. We project that approximately 4–5% of patients will be identified as high risk and thus eligible for the intervention. Utilizing a stepped-wedge cluster randomized controlled trial design, with > 50 clinics randomly assigned across three waves, we will assess the primary outcome, suicide attempts, at 90- and 180-days post-intervention. Given an anticipated suicide attempt rate of 0.6% (*n* = 2,370) within 90 days of a visit, a 0.01 intraclass correlation coefficient within waves, we expect to achieve more than 80% power (2-sided *p* <.05) to detect an effect size corresponding to a 1.5% absolute difference in suicide attempt rates [47–49].

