Generalized Linear Mixed Models (GLMMs) with logit link function will be used to assess categorical outcomes (identification and recognition, separately, defined as yes/no) to study the effect of the intervention on identification and recognition. The results will be presented as odds ratios (OR) with 95% CIs. We will analyze the frequency of events identified through PHQ-9 (identification), recognized through the C-SSRS (recognition), or both combined. Additionally, GLMMs with a log link function will be used to separately assess the effects on identification and recognition by modeling the count of identified or recognized patients. The model will include the intervention (yes/no) as an independent variable to assess its effect while accounting for clustering and potential confounders. Among visits where individuals are identified or recognized as being at risk, we will further investigate factors influencing these outcomes, including patient demographics and clinical characteristics. The results will be presented as relative risk (RR) with 95% CIs. In these analyses, clusters will be analyzed according to their randomized crossover time. Models will include a random effect for cluster and a fixed effect for each phase, and will adjust for age, sex, race/ethnicity and cluster/clinic terms (i.e., secular trend). These models are optimal and commonly used for studies implementing stepped wedge cluster randomized trial designs [31, 32, 50]. All analyses will also adjust for time, given that the ratio of exposed clinics increases over time, and calendar month to account for seasonality of suicide attempts. Given that patients may be screened or identified as at-risk multiple times, the frequency of visits during the follow-up period will be adjusted in the model as well. In additional analyses, the model will account for cluster effects by clinic and correlation between repeated measurements for the same patient over time.

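### The supplementary Cox models adjust for health system and calendar month but name no term for the randomized clinic, so as written their standard errors ignore clinic clustering

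*Protocol article*

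**What the plan says.** All references are to the Protocol article.

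- **Unit of randomization.** Overview of study design describes "randomization of behavioral health clinics into three waves across the three participating health systems". Exposure changes clinic by clinic: "Implementation begins when each randomized clinic (stratified by site) transitions from usual care to running the risk model".
- **Clustering in the sample size.** Sample size and power analysis assumes "a 0.01 intraclass correlation coefficient within waves". It gives no scale for this ICC.
- **GLMMs.** Analysis plan for effectiveness outcomes states "Models will include a random effect for cluster and a fixed effect for each phase". It later adds: "In additional analyses, the model will account for cluster effects by clinic and correlation between repeated measurements for the same patient over time". Similar GLMMs are then applied to engagement and suicide attempts.
- **Cox models.** The same section continues: "We will also use a Kaplan-Meier method and Cox-proportional hazards models to examine time-to-event for health service engagement and suicide attempts". The listed adjustments are clinical and demographic factors, followed by "We will again add terms for calendar month as well as site to account for variation by season and health system". Follow-up is censored at death or at 180 days after the index visit.

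No clinic stratum, clinic frailty, clinic covariate or clinic-robust variance is named for the Cox models.

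**The concern.** The Cox paragraph chooses a grouping level, the health system, that lies above the unit of randomization. A three-level site term removes differences between systems. It does not remove differences among the 10, 4 and 39 clinics within them.

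Clinics cross over at different times, so at any date the exposed and unexposed patients come from different clinics. Unless clinic is in the model, stable differences between clinics enter the exposed/unexposed contrast, and a standard error that treats patients as independent does not allow for it. Two results are exposed:

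- the hazard ratio for time to attempt, which could disagree with the clustered GLMM on the same event merely because of which clinics were drawn into the first wave;
- the hazard ratio for time to engagement. Objectives and hypotheses asks whether patients receive services sooner, and Cox is the only regression named for time to event.

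**Working it through.** **1. The plan's own figure.** 0.6% × 395,000 = 0.006 × 395,000 = 2,370 attempts, as stated. The plan gives no error rate for the Cox analysis, so the rest is a null check.

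**2. Inputs.** From the study-settings sections: 10 + 4 + 39 = 53 clinics, with about 50,000, 60,000 and 58,000 patients a year. From the sample-size section: 395,000 patients over 2.5 years (30 months), 0.6% event rate, ICC 0.01, two-sided 5%. Assumed: wave start months, between-clinic spread, 30% engagement, waves randomized within site.

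**3. What ICC 0.01 implies for clinics.** The text ties the ICC to waves and gives no scale. Applied to clinics:

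- Observed scale: CV² = ICC(1−p)/p = 0.01 × 0.994/0.006 = 1.66, so CV = 1.29. The log-normal SD is √ln(2.66) = 0.99, and the central 95% of clinics span exp(2 × 1.96 × 0.99), about 48-fold.
- Logit scale: variance = (0.01/0.99) × π²/3 = 0.033, so CV is about 0.18 and the 95% span about 2-fold. The equivalent observed-scale ICC is about 0.0002.

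**4. Closed-form check** (53 equal clinics, three waves, four periods, clinic ignored). At observed-scale ICC 0.01, the model SE is 0.00037 and the true SE 0.00198, a ratio of 5.37 before rounding. Rejection rate = 2Φ(−1.96/5.37) = 2Φ(−0.365) = 0.715. At ICC 0.0002, the ratio is 1.25 and the rate 11.6%.

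**5. Null simulation with the stated clinic counts and site volumes.** A rare-event Poisson equivalent of the Cox model, with site and all 30 months as terms, 400 replicates per cell. The first rate uses wave starts at months 12, 17 and 22; the second uses 8, 16 and 24, a wider spacing than the planned three to six months.

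| Outcome and clinic spread | No clinic term | Clinic-robust SE only | Term per clinic |
|---|---|---|---|
| Attempts, no clinic variation | 3.7%, 4.8% | 6.8%, 8.3% | 4.8%, 4.8% |
| Attempts, CV 0.10 | 8.7%, 10.0% | 9.5%, 9.8% | 6.2%, 7.0% |
| Attempts, ICC 0.01 logit scale | 14.2%, 20.3% | 9.8%, 10.5% | 3.7%, 4.5% |
| Attempts, CV 0.30 | 22.0%, 29.2% | 8.3%, 12.0% | 4.3%, 4.8% |
| Attempts, CV 0.50 | 43.0%, 53.2% | 14.0%, 10.5% | 6.8%, 5.2% |
| Attempts, ICC 0.01 observed scale | 69.0%, 78.0% | 13.8%, 17.5% | 6.0%, 4.5% |
| Engagement 30%, ICC 0.01 observed scale | 72.5%, 76.2% | 12.0%, 10.5% | 6.2%, 6.0% |

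Monte Carlo error is about 1 to 2.5 percentage points per cell. For engagement, the scale hardly matters: the logit-scale CV of 0.18 gives 72% and 78%.

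**6. If only flagged patients enter.** 4 to 5% of 395,000 is 15,800 to 19,750. From step 4, 5.37² − 1 = 27.8, so ratio² = 1 + 27.8 × (n/395,000) × (ICC/0.01).

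- Observed-scale ICC 0.01: √(1 + 27.8 × 0.04) = 1.45 and √(1 + 27.8 × 0.05) = 1.55, giving about 18 to 20%.
- Logit-scale ICC 0.01, n = 19,750, event rate still 0.6%: ratio = √(1 + 27.8 × 0.05 × 0.02) = 1.01, about 5%.
- The same with an assumed 5% event rate in flagged patients: observed-scale ICC = 0.183² × 0.05/0.95 = 0.00176, ratio = √(1 + 27.8 × 0.05 × 0.176) = 1.12, about 8%.

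**The case against.** **Silence is not exclusion.** The article never says that the Cox model treats patients as independent. The word *again* may carry over the GLMM structure, the section speaks of clinic effects in additional analyses, and a full analysis plan may settle the matter. What stands: the authors recognise clinic clustering, and an unseen document may already handle it. What does not: the sentence with *again* repeats only month and site, the sentence on additional analyses follows the GLMM text before Cox is introduced, and the article does specify the Cox adjustments, with a grouping level that is too high.

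**The Cox models are supplementary.** This stands in full. A reader might infer that the trial's primary result is at risk. The documents do not support that: the outcome is binary at 90 and 180 days, and the GLMMs lead and carry the cluster effect.

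**The largest figure is extreme.** This also stands. A reader might infer that about three null Cox analyses of attempts in four would come out significant under the plan's own ICC. That needs the observed scale, clinics rather than waves as the ICC's unit, all 395,000 patients in the model, and a roughly 48-fold spread in attempt rates between clinics. The plan states no scale and gives no support for such a spread.

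**The cohort is unclear.** The censoring rule counts from an index visit, which the outcomes section links to risk identification, while the primary denominator is all visits. With flagged patients only, the inflation for attempts shrinks, nearly to nothing in the mildest case.

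**Conclusion.** The point holds in a limited form. As written, the Cox models adjust at the level of the health system and omit the randomized clinic, unlike the GLMMs, so their intervals are too narrow whenever clinics within a system differ.

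With all patients in the model, the null rejection rate for attempts is about 9 to 10% at a clinic CV of 0.10, 14 to 20% at a logit-scale ICC of 0.01, and 69 to 78% only at the extreme observed-scale reading. For engagement it is about 73 to 76%, given an assumed 30% rate and ICC 0.01. With flagged patients only, attempts fall to about 18 to 20% at the observed scale. At the logit scale they lie between the nominal level and about 8%, depending on an event rate that the plan does not give.

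These sizes rest on applying an ICC worded for waves to clinics, on clinic differences that are stable over time, and on granting the Cox model site and time terms. The lead GLMM analysis of attempts is untouched. The plan should correct this, but it does not threaten the primary result.

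**What to change.** In Analysis plan for effectiveness outcomes, state that the Cox models will be stratified by clinic, or include a clinic frailty, with the same phase terms as the GLMMs.

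The clinic term is the essential part. With a term for each clinic, rejection for attempts was 4 to 7% in every scenario. Clinic-robust standard errors on their own left about 8 to 18% wherever clinics differed, because clinics are few and very unequal in size, so they would need a small-sample correction.

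The same sentence should say whether all patients or only flagged patients enter, and, if visits are the unit, how repeat visits by one patient are handled. Kaplan-Meier curves should be shown as description, without a log-rank p-value. If a separate analysis plan already specifies the clinic term, the text need only be aligned with it.

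The cost is one or two sentences and a standard software option; clinic must already be in the data for the GLMMs. The downside is a wider confidence interval than the independent-patient model would print.
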